## Introduction

1

Practitioners and researchers are focused on ageing and frailty, as demonstrated by different initiatives (1, 2). It has been shown that in the population older than 70 years, frailty represent a 5.5 times higher adjusted risk of mortality, a 2.5 times higher risk of new disability, and a 2.7 times higher risk of loss of mobility (3). To reduce frailty, action must be taken on its main risk factor, sedentary lifestyle (4), and the prevention of falls is thus of particular importance; falls are among the five main health problems related with disability in people older than 60 years (5).

Approximately 30% of people aged over 65% and 50% of those over 80 who live in the community have one fall once a year as a minimum (3, 5, 6). Similarly, about 30% of those who fall suffer a new fall in the same year and 10% suffer several falls (7). Falling is, therefore, a risk factor for further falls. Furthermore, Noureldin et al. found that 15% of hospitalised older adults people had a fall within 30 days of discharge (8).

Falls represent a major cause of disability in older adults and over 50% present sequelae (5, 6); half of those suffering a fracture from a fall do not fully recover their previous functional level. Older adults are admitted to hospital for injuries related to falls more frequently and they also present discharges and consecutive readmissions over the following three years (8, 9). Besides, between 32% and 80% of patients who survive hospitalisation after a hip fracture are left with a permanent disability (10), being a 95% of hip fracture cases a result of falls (11). In this regard, it has been observed that physical exercise approaches can reverse the functional disability caused by hospitalisation in older patients (12).

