### Sample size

3.3

The main variable of the study was used to estimate the sample size, the annual incidence rate of falls in this population. An alpha risk of 0.05 and a beta risk of 0.2 (Power for Chi square 80% and t-test 94%), effect size estimated 0.30 (Cohen D) and 0.01 (V de Cramer) in a two-sided contrast has been accepted, 325 participants in the intervention group and 325 in the control are needed to find differences of ten percentage points as statistically significant between the control group, expected to be 30% [the estimate of falls in people older than 65 years of age (3, 5, 6)] and the intervention group, expected to be 20%. A give up rate of 10% during follow-up has been estimated.

This data has been calculated following the formula for qualitative variables published by Argimon Pallàs et al. (25).

$N=\frac{Za.Ö\;2.p.\left(1-p\right)+ZbÖ\;p1.\left(1-p1\right)+p2.\left(1-p2\right)2}{\left(p1-p2\right)2}$

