### Statistical analysis

3.9

The study population baseline characteristics will be expressed as means ± standard deviation (SD) for quantitative variables and in frequency distributions for categorical variables. Student’s t-test, chi-square, and Fisher’s exact tests will be applied to find differences in baseline characteristics between intervention and control groups. All analyses of the variables obtained from the questionnaires will be analyzed using the reliability and validity criteria proposed by their authors.

The main analyses will be performed on the intention-to-treat principle, so all randomised subjects will be included in the data analysis set for which the initial assessment was performed. Participants who withdraw or drop out will be asked to be included in follow-up measurements; those lost to follow up will be considered in the full set of analyses as missing data. Detailed modelling of variations between participants and groups will be done in terms of factors such as dose, acceptability, and contextual factors. Using the Chi-square test, we will compare the proportions of subjects who have had a fall in both groups. The comparison of all outcomes between baseline, six and twelve months will be carried out using the two-way repeated measures ANOVA. Logistic regression analysis will be conducted to determine the influence of the different risk factors on falls. Statistics analysed will be performed with SPSS V.25.0 statistical package (SPSS Inc., Chicago, Illinois, United States). *p* values for cut-off values for significance were established at <0.05 (two-tailed). Results were interpreted according *[Cohen]*, who considers small size if Cohen D are between 0.2 ≤ and < 0.5; average effect size if differences are between 0.5 ≤ and < 0.8 and very high effect size if differences are ≥0.8 (38).

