### Limitations

4.1

The 24 months prior to data collection could be a long period to remember such events for such individuals. In this study the interview will be complemented with the information available in the participants’ primary care medical history and in the records of the University Hospital “X” to ensure that all falls which had consequences are considered.

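### Cheap improvement: the arm comparison on falls is an unadjusted chi-square that leaves previous falls unused, although the protocol calls them a risk factor and implies that they are recorded

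*Protocol article*

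**What the plan says.** - **Test of the arm effect** (protocol article, section 3.9): "Using the Chi-square test, we will compare the proportions of subjects who have had a fall in both groups". No covariate or stratification is mentioned for this comparison.
- **Other model on falls** (section 3.9): "Logistic regression analysis will be conducted to determine the influence of the different risk factors on falls". The article does not say that this model estimates the effect of arm.
- **Prognostic factor** (section 1, Introduction): "Falling is, therefore, a risk factor for further falls".
- **Evidence that a history is taken** (section 4.1, Limitations): "The 24 months prior to data collection could be a long period to remember such events for such individuals". The next sentence says that the interview is supplemented from primary care and hospital records.
- **Baseline items** (sections 3.4 and 3.7): previous falls are not named in the content of the initial visit or among the variables.
- **Allocation** (section 3.5): 1:1, with no stratification described.
- **Outcome** (section 3.7.8): falls are logged daily and the log is sent in monthly.

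**The concern.** A baseline value that the protocol itself regards as predictive of the outcome, and that it appears to collect, plays no part in the stated comparison of arms. Eligibility neither requires nor excludes earlier falls, so the sample will mix fallers and non-fallers, and no stratification is described that would balance them.

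Two modest things are at stake. Some precision is given up. And if previous fallers happen to be unevenly split, the unadjusted difference moves with the imbalance. Section 3.9 tests baseline differences between the arms but attaches no consequence to them, so an adjustment made after seeing an imbalance would be post hoc and open to challenge.

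There is also a point of wording. Because 4.1 does not say which falls the 24-month recall concerns, a hurried reader could take it to describe the outcome.

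**Working it through.** **Inputs from section 3.3.** "An alpha risk of 0.05 and a beta risk of 0.2", "in a two-sided contrast has been accepted"; control proportion 0.30 ("statistically significant between the control group, expected to be 30" per cent); intervention proportion 0.20 ("the intervention group, expected to be 20" per cent); 325 per arm; 10% dropout.

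**Inputs that are assumptions.** The proportion of previous fallers (30%) and the odds ratio (OR) linking previous falls to falls in the trial (2, 3, 4). The documents give no such association. The introduction's figure that about 30% of fallers fall again concerns the same year and cannot supply it.

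**1. Reproduce the sample size.** With a pooled proportion of 0.25:

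n = [1.96 × √(2 × 0.25 × 0.75) + 0.842 × √(0.3 × 0.7 + 0.2 × 0.8)]² / 0.10² = (1.200 + 0.512)² / 0.01 ≈ 293.2, so 294 per arm.

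With 10% dropout: 294 / 0.9 = 327, or 294 × 1.1 = 324. The stated 325 is reproduced. Evaluable: 325 × 0.9 = 292.5, so 292 per arm, with power of about 80%.

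**2. Risks by fall history.** Solve 0.7·r0 + 0.3·r1 = arm risk, with the odds of r1 equal to OR times the odds of r0.

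| OR | Control r0, r1 | Intervention r0, r1 | Mean gradient (points) |
|---|---|---|---|
| 2 | 25.5%, 40.6% | 16.5%, 28.3% | (15.1 + 11.8)/2 = 13.5 |
| 3 | 22.8%, 46.9% | 14.3%, 33.3% | (24.2 + 19.0)/2 = 21.6 |

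(Gradients use unrounded risks.)

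**3. Chance imbalance.** SD of the difference between arms in the proportion of previous fallers = √(2 × 0.3 × 0.7 / 292) = 0.038. The 95% limit is 1.96 × 0.0379 = 7.4 points. Shift in the unadjusted risk difference at that limit:

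- OR 2: 0.0743 × 13.5 = 1.0 point
- OR 3: 0.0743 × 21.6 = 1.6 points

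At one SD the shifts are 0.5 and 0.8 points. For scale, the standard error of the risk difference is √((0.21 + 0.16)/292) = 3.6 points.

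**4. Precision and power.** The unadjusted variance is 0.37/292. The adjusted variance keeps only the variation within history groups, plus a small term for the risk difference varying between them:

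{Σ over arms [0.7·r0(1−r0) + 0.3·r1(1−r1)] + 0.3 × 0.7 × (difference in gradients)² / 2} / 292.

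For OR 2 the bracket is 0.2052 + 0.1571 + 0.0001 = 0.3624, and 0.3624/0.37 = 0.979, a reduction of 2.1%. The same steps give 5.3% at OR 3 and 8.5% at OR 4.

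| OR | Power, large-sample formula | Power, simulated stratified test |
|---|---|---|
| unadjusted | 80.2% | about 80% |
| 2 | 81.0% | about 80.5% |
| 3 | 82.3% | about 82% |
| 4 | 83.6% | about 83% |

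The two methods agree to about half a point. In participants, the variance reductions correspond to 0.021 × 650 ≈ 14 at OR 2 and 0.053 × 650 ≈ 34 at OR 3.

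**5. Sensitivity.** Varying the proportion of previous fallers from 20% to 50% hardly matters: by the formula, power stays at about 81% for OR 2, 82% for OR 3 and 83 to 84% for OR 4. In simulation without an effect, both tests kept a type I error of 4.3 to 5.3%.

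**The case against.** The strongest reply is that nothing here is wrong. The chi-square in a randomised trial is valid, holds its type I error and is the test behind the 325 per arm. Chance imbalance is not bias, and the p-value and confidence interval already allow for it. Even at its 95% limit the shift is only about 0.3 to 0.45 of a standard error (1.0/3.6 and 1.6/3.6). The gain at OR 2 is about half a point of power, and error in recalling 24 months would reduce it. All of that stands, and it is why this is only a cheap improvement.

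It is also true that collection of fall history is inferred from one sentence in Limitations. That sentence and the next resemble the account of the initial interview and records in section 3.4, which supports reading it as baseline history, but the item is not listed. The gain is therefore not strictly free.

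A further reply is that covariates are usually left to the analysis plan, and that the logistic regression in 3.9 might include arm and previous falls. The article does not exclude this. But it does name the test for the arm comparison, and the remark here is about that stated choice, not about missing detail.

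A reader might also infer that 4.1 contradicts the prospective daily log in 3.7.8. It does not: read as baseline history, the 24-month recall and the log concern different falls. The sentence is loose, no more.

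**Conclusion.** The point holds as a low-cost improvement. A prespecified adjustment for previous falls would raise power from about 80% to roughly 80.5%, 82% or 83% at odds ratios of 2, 3 or 4. It would also largely remove a shift of about 1.0 to 1.6 points at the 95% limit of imbalance (OR 2 to 3). These sizes rest on an assumed 30% of previous fallers, assumed odds ratios, 292 evaluable per arm, and a history recorded with reasonable accuracy.

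A reader might go further and conclude that the planned test is invalid or the trial underpowered. The documents do not support that, because the sample size reproduces for exactly this test. It would likewise be too strong to say that the history is certainly at hand, or that the plan forbids adjustment. Nor should the imbalance at its limit be read as the expected case: the 80% already averages over imbalances in both directions.

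**What to change.** 1. List previous falls (yes/no, one stated recall window, with a category for missing) as a baseline item in sections 3.4 and 3.7.
2. In 3.9, make the arm comparison on falls a prespecified logistic model with arm and previous falls. Report one effect measure, the standardised risk difference with its 95% CI, which is on the scale of the 10-point target. Keep the unadjusted chi-square as a sensitivity analysis.
3. In 4.1, say that the 24-month recall refers to baseline history and not to the logged outcome.

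The cost is some wording, at most one interview item, and a rule for missing history. The sample size need not change.

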**Objective:**

To measure whether a group intervention with the strength and balance principles of the sLiFE program is more effective than standard health advice in reducing the incidence of falls.

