**Methods:**

The study will comprise 650 participants with more than 65 years who live at home, observing established inclusion and exclusion criteria. Participants will be randomly assigned in two groups: group intervention (*n* = 325) and standard health advice (*n* = 325). The intervention group will follow the balance and strength activities described in the LiFE program manual. The group intervention will be carried out in groups of 12–14 and will consist of seven one-hour sessions over 12 weeks in health centres. Incidence of falls and quality of life will be assessed as primary outcome variables. Fear of falling and exercise adherence will be analysed as secondary outcome variables.

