#### Primary outcome measures

3.7.8

The incidence rate of falls will be estimated based on the intervention and control group. Falls will be recorded using a daily log sent to the study centre monthly. On suffering a fall, participants must provide information about the time, date, injuries and prescribed treatment in relation to the fall, the fall location, and the movement which cause the fall. The person will be interviewed by telephone to correct any lack of data to determine the injuries details and to confirm their health status at this time (7).Quality of life will be measured through the EuroQol 5D questionnaire, validated in Spanish (34). This questionnaire comprises five items (mobility, personal care, daily activities, pain/discomfort, and anxiety/depression) and a self-assessed thermometer of health status.

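### The ANOVA for quality of life and fear of falling names no effect as the test of sLiFE; a baseline-adjusted arm difference would be clearer and at least as powerful, at no cost

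*Protocol article*

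**What the plan says.** The trial's question is between arms. The abstract's objective asks whether the group programme "is more effective than standard health advice in reducing the incidence of falls", and section 2 states the hypothesis in the same terms. The abstract's methods say: "Incidence of falls and quality of life will be assessed as primary outcome variables". Section 3.7.8 repeats this by listing quality of life under the primary outcomes: "Quality of life will be measured through the EuroQol 5D questionnaire, validated in Spanish". Fear of falling (Short FES-I) is secondary, in section 3.7.9.

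Section 3.9 gives falls an explicit between-arm test, a chi-square test on the proportion of fallers. For everything else it says: "The comparison of all outcomes between baseline, six and twelve months will be carried out using the two-way repeated measures ANOVA". The t-tests in that section are for baseline characteristics. The modelling of variation between participants and groups names no model. So this one sentence carries the whole analysis of EuroQol 5D and the Short FES-I.

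On visits, section 3.9 uses baseline, six and twelve months. Section 3.6.4 lists a follow-up evaluation at six months only. Section 3.8 describes one reassessment, six months after the initial assessment for controls and six months after the sessions end for the intervention arm.

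**The concern.** A two-way repeated measures ANOVA with arm and visit as factors gives three F tests, which answer different questions.

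- **Time:** has the mean of both arms pooled changed? This is the contrast closest to the sentence's wording, and it says nothing about sLiFE.
- **Group:** do the arms differ on average over all visits? The average includes the pre-randomisation visit, where the true difference is zero, so a constant effect is diluted.
- **Group by time:** does the pattern over visits differ between arms? This one bears on sLiFE, but the sentence does not name it.

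At stake is how a primary outcome will be judged. Without a designated effect, the reader cannot tell which F test will be the result. Even the relevant one gives no arm difference with a confidence interval at any visit, and it makes less efficient use of a baseline value that the trial already collects.

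**Working it through.** **1. The plan's own sample size.** Section 3.3 says "325 participants in the intervention group and 325 in the control are needed to find differences of ten percentage points", for 30% against 20%, two-sided alpha 0.05, power 80% and 10% dropout. With a pooled proportion of 0.25:

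n = [1.960·√(2·0.25·0.75) + 0.842·√(0.30·0.70 + 0.20·0.80)]² / 0.10² = 293.15

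293.15 / 0.90 = 325.7. The stated 325 is reproduced. Complete cases per arm: 325 × 0.90 = 292.5, taken as 292.

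**2. Assumptions.** The article gives no effect size, SD or visit correlation for EuroQol 5D or the Short FES-I. The Cohen's d of 0.30 in section 3.3 is not tied to either. I therefore assume SD 1, equal correlation ρ between visits (0.5 and 0.7), complete data, and the same arm effect δ at both follow-ups (0.2 and 0.3 SD). Three visits are used, as section 3.9 states.

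**3. Formulas, n = 292 per arm.**

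- Interaction (2 and 1,164 df): noncentrality λ = nδ² / [3(1−ρ)]
- Group main effect: estimate 2δ/3, SE = √[(2/n)(1+2ρ)/3]
- Baseline-adjusted arm contrast at one visit: estimate δ, SE = √[(2/n)(1−ρ²)]
- Baseline-adjusted arm contrast on the mean of both follow-ups: estimate δ, SE = √[(2/n)((1+ρ)/2 − ρ²)]

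**4. Worked case, δ = 0.2, ρ = 0.5.**

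- Interaction: λ = 292·0.04/(3·0.5) = 7.79, power 70%
- Group: 0.133/0.0676 = 1.97, power about 50%
- Adjusted, one visit: 0.2/0.0717 = 2.79, power 80%
- Adjusted, follow-up mean: 0.2/0.0585 = 3.42, power 93%

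**5. Power across the assumptions.**

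| δ | ρ | Group | Interaction | Adjusted, one visit | Adjusted, follow-up mean |
|---|---|---|---|---|---|
| 0.2 | 0.5 | 50% | 70% | 80% | 93% |
| 0.2 | 0.7 | 44% | 91% | 92% | 98% |
| 0.3 | 0.5 | 84% | 97% | 99% | over 99% |
| 0.3 | 0.7 | 77% | 99.9% | 99.9% | over 99.9% |

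**6. If there is only one follow-up visit.** The interaction then reduces to comparing change scores, with SE = √[(2/n)·2(1−ρ)]. For δ = 0.2 its power is 68% at ρ = 0.5 (0.2/0.0828 = 2.42) and 88% at ρ = 0.7 (0.2/0.0641 = 3.12). The adjusted contrast has 80% and 92%. The ordering does not depend on the twelve-month visit.

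**7. Error rates with no arm effect.** Simulated trials (293 per arm, ρ from 0.4 to 0.8, shared change 0 to 0.3 SD in both arms, 2,000 runs per setting) gave rejection rates of 4.5% to 6.1% for the interaction and 3.9% to 5.7% for the group effect. Both are near the nominal 5%. Only the pooled time effect rejects more often, about 80% for a shared 0.10 SD change at ρ = 0.6, because it correctly detects a change that is unrelated to arm.

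**The case against.** A reader might infer from the wording that the null being tested is no change over time, so that a change common to both arms would count as a result for sLiFE. The documents do not support that. The sentence says two-way; a comparison of visits alone would be one-way. Section 3.1 describes two parallel arms, so arm is the natural second factor. The hypothesis and the falls sentence just before it both concern arms. The list of visits can be read as the levels of the repeated factor. Nothing in the article designates the pooled time effect as the result, so its high rejection rates are not an error rate of this trial.

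It can also be said that group-by-time ANOVA is a valid standard analysis, that the power gap depends on assumed values and nearly vanishes at 0.3 SD, and that an article may leave the choice of F test to an analysis plan that is not shown.

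Most of this stands. It removes any claim of a wrong null or an inflated error rate, and leaving the deciding F test unnamed is not by itself a fault. It does not remove the case for a better method. The article names its method, and an adjusted arm contrast answers the trial's question directly, with an estimate and interval. In none of the settings computed does it have less power.

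**Conclusion.** A free improvement. Section 3.9 gives a primary outcome and a secondary outcome a method worded as a visit comparison, without saying which effect tests sLiFE. On the charitable reading the test is valid, but it is an omnibus test with no arm estimate.

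Under the assumed 0.2 SD effect with 292 per arm, the interaction falls 10 points short of a one-visit adjusted contrast and 23 short of one on the follow-up mean at correlation 0.5. At correlation 0.7 it falls 1 and 7 points short. At 0.3 SD the loss is at most about 3 points. The group main effect is the weakest choice throughout, and the pooled time effect is uninformative about sLiFE. Effect, correlation, equal effects at both follow-ups and complete data are assumptions and not figures from the article.

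**What to change.** In section 3.9, replace the ANOVA sentence for EuroQol 5D and the Short FES-I with wording such as: *The arms will be compared by the difference in mean follow-up score, adjusted for the baseline value of the same measure (ANCOVA, or a model with arm-by-visit terms and baseline as covariate), and reported with a 95% confidence interval. Changes over time within or across arms are descriptive and do not support a claim of effect.*

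Then name the follow-up visit, or the mean of the follow-ups, that carries the primary quality-of-life comparison. Twelve months should not be written in until sections 3.6.4 and 3.8, which describe only a six-month assessment, are reconciled with the six and twelve months in section 3.9.

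The cost is two or three sentences. Section 3.4 already collects the baseline values, the stated SPSS package runs these models, and no participants or measurements are added.

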#### Secondary outcome measures

3.7.9

Fear of falling: Short Falls International Scale of Efficacy (Short FES-I) assess “concerns about falling” (35). The scale is the falls efficacy scale-international short version, comprising seven items (items 2,4,6,7,9,15 and 16). Item responses are coded on a 4-point Likert scale: (1) not at all concerned, (2) somewhat concerned, (3) fairly concerned, and (4) very concerned.Exercise adherence will be measured using the Exercise Adherence Rating Scale (EARS) as part of the schedule sent in monthly. This scale is composed of 16 items, scored using a 5-point Likert scale (0 = completely agree to 4 = completely disagree) with a total summed score range from 0 to 64 (36).Cost-effectiveness of the intervention: Incremental cost-effectiveness ratio (ICER) related with the ratio of the difference in costs to the health effects difference in both interventions (37). These costs include outpatient treatment, formal/informal care, medication, transportation, room rental, intervention costs involving labour costs, staff and participants transportation, and materials.

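### The repeated measures ANOVA named for the primary EQ-5D analyses only participants with every visit, so in effect it does not deliver the stated intention-to-treat set, and it uses baseline inefficiently

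*Protocol article*

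**What the plan says.** All references are to the protocol article.

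- **Method.** Statistical analysis (3.9): "The comparison of all outcomes between baseline, six and twelve months will be carried out using the two-way repeated measures ANOVA". EQ-5D is listed under Primary outcome measures (3.7.8) and Short FES-I under Secondary outcome measures (3.7.9). No other between-arm test is named for either.
- **Analysis set.** The same section adopts intention-to-treat and says "all randomised subjects will be included in the data analysis set for which the initial assessment was performed". People lost to follow-up are to count as missing data. No imputation or likelihood-based method is named.
- **Withdrawals.** Procedures (3.8) keeps the data collected before a withdrawal, unless the participant asks for deletion.
- **Expected loss.** Sample size (3.3): "A give up rate of 10% during follow-up has been estimated".
- **Visits.** Stage four (3.6.4) and Procedures describe a reassessment at six months only. Neither mentions twelve months.
- **Falls.** Statistical analysis gives the proportion of fallers a chi-square test and examines risk factors for falls by logistic regression.
- **Adherence.** Section 3.7.9: "Exercise adherence will be measured using the Exercise Adherence Rating Scale (EARS) as part of the schedule sent in monthly". Participant assessment (3.4) also lists adherence to exercise among the data taken at the initial visit.

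**The concern.** A protocol may leave missing-data detail to an analysis plan. Here, however, the article fixes a method, and that method determines who is analysed. Classical repeated measures ANOVA needs a complete row per person. Someone with baseline and six-month values but no twelve-month value is deleted, earlier data included. That is hard to square with a set of all randomised participants who had an initial assessment, or with keeping pre-withdrawal data.

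A primary comparison is at stake. Participants are not blinded, and the abstract itself calls long-term adherence a challenge, so dropout related to response, and differing by arm, is plausible. A completer comparison is then open to bias.

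A second, smaller weakness is that the ANOVA treats baseline as one more outcome. With a single follow-up its group-by-time test is a test of change scores, which is less precise than adjusting for baseline.

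**Working it through.** **1. The plan's own figure.** Inputs from Sample size: 30% against 20% with a fall, "An alpha risk of 0.05 and a beta risk of 0.2", two-sided, 10% loss. With p = 0.25 as the pooled proportion:

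n = [1.96·√(2·0.25·0.75) + 0.8416·√(0.30·0.70 + 0.20·0.80)]² / 0.10² = (1.200 + 0.512)² / 0.01 ≈ 293.2, so 294 per arm.

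Allowing for loss, 294/0.90 = 327 and 294 × 1.1 = 324. The stated 325 per arm is reproduced, so the size already allows for 10% loss.

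**2. Who is left in the ANOVA.**

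- 10% miss at least one visit: 0.10 × 650 = 65 excluded. By arm, 325 × 0.90 = 292.5, rounded down to 292, so about 584 are analysed.
- 10% independently miss each of two follow-ups (assumed): 0.90² = 0.81, and 650 × 0.81 = 526.5, so about 526 are analysed and 124 excluded.
- 20% miss at least one visit (assumed): 130 excluded.

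**3. Power.** Two-sample comparison at d = 0.30, the protocol's standardised effect: 0.969 at 325 per arm, 0.952 at 292, 0.931 at 263 and 0.928 at 260. The protocol states 94% for its t-test. The loss of power is small.

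**4. Bias.** Illustrative simulation, with every setting assumed: 325 per arm; true effect 0.30 SD at six and twelve months; correlations 0.5 (baseline with each follow-up) and 0.7 (between follow-ups); everyone seen at six months; dropout before twelve months. In the selective rows, the log-odds of dropout change by 1 per SD of six-month change. The estimate is the arm difference in change from baseline to twelve months.

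| Dropout | Loss | No loss | Completers | All available data |
|---|---|---|---|---|
| Completely random | 10% | 0.298 | 0.297 | 0.298 |
| Poor responders leave, both arms | 10% | 0.293 | 0.278 | 0.292 |
| Poor responders leave, both arms | 20% | 0.299 | 0.279 | 0.302 |
| Opposite directions by arm | 10% | 0.300 | 0.428 | 0.301 |
| Opposite directions by arm | 20% | 0.297 | 0.539 | 0.297 |

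The mechanism matters. With all correlations at 0.6 and dropout driven by the six-month level, in opposite directions by arm, completers showed no bias at 10% loss (0.305 with and without loss).

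**5. Baseline handling, one follow-up.** Take equal variance s² at both times and correlation r. The change score has variance 2(1−r)s². The baseline-adjusted residual has variance (1−r²)s². The ratio is (1−r²)/[2(1−r)] = (1+r)/2, which is 0.75 at r = 0.5 and 0.85 at r = 0.7. The protocol gives no r.

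**6. Visits.** The ANOVA has three time levels. Stage four and Procedures supply two: the initial assessment and one at six months. Procedures counts the six months from the initial assessment in controls and from the end of the sessions in the intervention arm. With a twelve-week programme, that is roughly nine months after the start of sessions.

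**The case against.** The strongest reply is that nothing in the wording contradicts intention-to-treat. The section defines the set and invites those who withdraw to continue follow-up measurements; imputation before the ANOVA would remove the problem, and that detail may sit in an analysis plan not shown. This stands in part. The conflict is one of effect, and silence about imputation is not itself a fault. What remains is that the stated method, applied with losses left missing, yields completers.

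Other points that stand:

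- The 10% loss is already in the sample size, and the power cost is slight.
- With complete data, the change comparison is valid in a randomised trial. Baseline adjustment is a gain in precision, not the repair of an error.
- The 15–25% variance reduction is for one follow-up, not for the three-level ANOVA as written.
- A mixed model fitted to post-baseline values only, with baseline as a covariate, would also lose anyone without a follow-up value. With a single reassessment it would drop the same 65 or so people.

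A reader might also infer that falls will be judged by ANOVA, since the sentence covers all outcomes. The preceding sentence gives falls a chi-square test and the following one a logistic regression, so that reading is not supported; the wording merely fails to exclude it. A reader might likewise infer that adherence has no baseline value, but the initial visit lists it. The protocol gives no ground for requiring that EARS be analysed in the intervention arm alone.

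**Conclusion.** The point holds in a limited form. For EQ-5D and Short FES-I the named ANOVA gives a completer analysis. In effect it delivers neither the stated intention-to-treat set nor the promised use of pre-withdrawal data. About 65 of 650 are excluded at the planned loss, more if different people miss different visits.

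The main harm is possible bias. Its size is unknown: the 0.43 and 0.54 estimates need dropout running in opposite directions by arm and are not forecasts. The precision cost, a variance ratio of 0.75 to 0.85, assumes one follow-up, equal variances and r between 0.5 and 0.7.

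The sample size is unaffected. The change should be made because it concerns a primary outcome and costs little.

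**What to change.** For EQ-5D and Short FES-I, replace the ANOVA sentence with a likelihood-based linear mixed model fitted to all available values. Keep baseline in the outcome vector with its mean constrained equal between arms, and include visit and arm-by-visit terms, with arm differences only after baseline. Every randomised participant with a baseline value then stays in the analysis. Report the arm difference with its 95% CI at one named follow-up visit.

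Reconcile the twelve-month level in Statistical analysis with the six-month assessment in Stage four and Procedures, including the different starting points of the six months by arm. State that falls are outside this sentence, since they are analysed separately.

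If there is only one follow-up, the model is close to ANCOVA. The gain is then mainly precision, and validity when missingness depends on baseline. It does not recover outcomes for people with no follow-up.

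The cost is a change of wording, slightly more analysis work and a missing-at-random assumption. No extra participants or visits are needed, and the named software fits mixed models. Trial status describes invitations still under way, so at the time of writing this could be settled before outcome data were seen.
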